### Outcomes

The primary outcome of this RCT is that bracing will be considered potentially effective, if after two years the mean progression of the abnormal curvature in the intervention group is at least 5 degrees less than in the control group. Two years after date of randomization the primary outcome measure, progression in Cobb angle, will be established in each patient. Mean Cobb angles, as reported independently, in the intervention arm will be compared to mean Cobb angles in the control arm. To reduce inter-observer measurement errors, two orthopedic surgeons associated with the project team will judge all X-rays independently and without knowledge of the allocation arm. The mean value of the observed Cobb angles will serve as assessed value, whenever the difference between the two measurements is less than 3 degrees. If the difference is larger, a third orthopedic surgeon will be asked to measure the Cobb angle; the mean Cobb angle of all 3 measurements will serve as the assessed value.

The secondary outcomes of this study concern health-related quality of life (HRQoL) and compliance to brace treatment. Because bracing is a burdensome procedure (including reduced activity in daily living, pain, and implications for self-esteem, satisfaction with appearance, and mood), HRQoL will be evaluated in the intervention and control group by a generic HRQoL questionnaire, i.e. Child Health Questionnaire-Child Form 87 items (CHQ-CF87) and the Child Health Questionnaire-Parent Form 50-items, (CHQ-PF50) EuroQol including a VAS for general health, and a disease-specific questionnaire, i.e. the adjusted Scoliosis Research Society-22 Patient Questionnaire for Idiopathic Scoliosis (SRS-22r Patient Questionnaire). These questionnaires have been translated into Dutch; score distribution and internal consistency corresponded with the original versions [14-16]. Patients will be asked to fill out the CHQ-CF87, EuroQol and SRS-22 Patient Questionnaire just before every other visit to the orthopedic surgeon, thus 4 times in total. The EuroQol scores can be translated into utilities with values from the Dutch general population. The parents of the patients are requested to fill out the CHQ-PF50, EuroQol and SRS-22 at the same time that their child fills out her/his questionnaires. Patients and parents will receive the questionnaires and a return envelope about two weeks before every other visit to the orthopedic surgeon; thus they can fill out the questionnaires before they know the results of the X-ray (i.e., before knowing whether or not the curvature has progressed).

IS patients are usually advised to wear the brace for 18–23 hours every day as long as the patient is growing, which often implies wearing the brace during many years in adolescence. Hence, the risk of non-compliance is present. Lack of compliance in this group would lead to an underestimation of the treatment effect, if present, and would reduce the power of the trial. Compliance will be measured by three different means. The orthopedic surgeon will ask the patients and their parents how many hours a day the patients wear the brace. Because the patient has to return every 4 months for a check-up, the brace will be checked for signs of wear and tear typical for an intensively-used brace. Besides this, patients of the intervention group will receive a short questionnaire in which compliance, attitudes, social influences and barriers to wearing the brace will be measured at every other visit to the orthopedic surgeon.

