### Objectives

The purpose of this RCT is to establish whether brace treatment in IS patients with Cobb angles between 22 and 35 degrees significantly reduces further bending of the spine, thereby preventing surgery for some patients. The specific research questions are:

1. Will bracing patients with IS in an early stage result in at least 5 degrees less mean progression of the curvature compared to the control group after two years of follow-up?

2. Do differences in health-related quality of life exist between patients with IS who are treated with a brace and patients who are under watchful waiting?

3. If bracing proves to be effective, what is the cost-effectiveness of brace treatment, compared to regular surveillance only in terms of cost per avoided surgery and cost per QALY, accounting for the (increased) burden of bracing and the (reduced) burden of surgery? If bracing does not appear to be effective, what are the possible savings if treatment guidelines would be changed?

4. If bracing proves to be effective, what is the cost-effectiveness of the nationwide screening program for scoliosis?

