### Sample size

The Cobb angle at inclusion will on average be 29 degrees (range 22–35 degrees). Due to the standard error of radiographic production and intra and inter-observer measurement variation, a measurement error in Cobb angles of 5 degrees will appear [1]. To reduce the standard error of radiographic production, all patients will undergo X-ray following a strict protocol. Because inter-observer measurements errors are reduced (see *Outcomes*), measurement error will than be maximal 2 degrees, thus the 95% observation interval of Cobb angles at inclusion is 20–37 degrees. After two years, when the outcome will be determined, the range in change will be 0–15 ± 2 degrees. Assuming a uniform distribution of this change in Cobb angle between the patients after two years (most unfavorable scenario), the standard deviation of the difference in change between baseline and outcome measurement will be about 4.5 degrees.

Since bracing has to be better than observation to be justified as treatment for IS, a superiority design will be used. With a power of 95% and alpha = 0.05, a mean difference of 5 degrees between the groups can be detected with 40 patients in both study arms. We will aim at a study population at start of 100 patients to take loss to follow-up into account.

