## Discussion

In collaboration with Dutch orthopedic surgeons we have designed the first randomized controlled treatment trial and started it in 2006. In 2007, dr. Weinstein et al. also started a randomized controlled treatment trial on bracing in the USA (BrAIST) [17]. The results of these trials will be of great importance to the discussion on bracing patients with IS. At the moment, patients and parents face a dilemma, because the only available treatment has not been proven effective, and is a rather burdensome one.

The results of this study will also be valuable for the screening program for scoliosis. Screening aims at detecting scoliosis in an early stage of the clinical course to allow brace treatment to try and prevent further progression of the curvature and reducing the need for surgery [11]. Recently, we performed a case control study on the effectiveness of screening for scoliosis. In that study, the case group consisted of surgically treated IS patients (the condition screening and early treatment should prevent) and the control group consisted of a random sample of Dutch youth. We found no evidence that cases were significantly less screened than controls [18]. If we had found a positive effect of screening, that would have implied that bracing is effective. A RCT on the effectiveness of bracing now seems even more justified. If bracing shows to be effective, the screening program needs to be revised. If bracing doesn't prove to be effective, a screening program is not applicable, since the availability of an effective early treatment is one condition for a screening program to be justified [19].

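### The 95% power is for detecting a true 5-degree difference against zero; it does not apply to the stated criterion of a difference of at least 5 degrees, which has a 50% chance of being met at a true 5

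*Protocol article*

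**What the plan says.** The protocol article uses 5 degrees in two roles.

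- **As the criterion for effect.** Outcomes presents this as the primary outcome. The two-year condition for regarding bracing as potentially effective reads "the mean progression of the abnormal curvature in the intervention group is at least 5 degrees less than in the control group". Research question 1 in Objectives asks whether bracing will "result in at least 5 degrees less mean progression of the curvature compared to the control group after two years of follow-up". The aim in the Abstract carries the same threshold.
- **As the difference to be detected.** Sample size states that "a mean difference of 5 degrees between the groups can be detected with 40 patients in both study arms", the error rates for this being given as "With a power of 95% and alpha = 0.05". The SD behind this is given as follows: "the standard deviation of the difference in change between baseline and outcome measurement will be about 4.5 degrees". The design is described as superiority, because bracing has to be better than observation, and no margin is given.

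Statistical methods plans ordinary parametric or non-parametric group comparisons and no test against a 5-degree null. The opening sentence of Objectives asks whether bracing significantly reduces further bending, which is a comparison with zero. No section connects the two roles or says how a significant difference below 5 degrees would be read.

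**The concern.** A power statement should give the chance that the trial meets its own criterion when the planning assumption is true. Here the criterion is a mean difference of at least 5 degrees, while the power concerns rejecting a difference of zero when the truth is 5. A reader who puts the two sections together will take it that a brace truly worth 5 degrees has a 95% chance of meeting the criterion. It has not.

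What is at stake is the primary conclusion. Over a range of plausible results, the significance test and the 5-degree criterion give different answers, and the article does not say which governs. Research question 3 then splits on whether bracing proves effective, so the ambiguity carries into the economic question.

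**Working it through.** **Inputs.** From Sample size: difference 5 degrees, SD 4.5, alpha 0.05, power 95%, 40 per arm, 100 enrolled (50 per arm at the 50–50 allocation in Table 2). The article does not state whether alpha is one- or two-sided; two-sided is assumed, with one-sided where shown. The normal approximation is used.

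**1. The plan's own figure.**
n per arm = 2 × (1.96 + 1.645)² × 4.5² / 5² = 21.05, so 22 (one-sided 18), not 40.
With 40 per arm, SE = 4.5 × √(2/40) = 1.006, and power against zero at a true 5 = Φ(5/1.006 − 1.96) = Φ(3.01) ≈ 99.9%.
For 40 per arm to give 95% power, the SD must be 5 × √20 / (1.96 + 1.645) = 6.20 (one-sided 6.80).
The stated 40 is therefore not reproduced from SD 4.5. That is a separate matter, but it means that any result depending on the SD should be shown for both 4.5 and 6.2.

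**2. Chance of meeting the criterion at a true 5.**
P(observed ≥ 5 | true d) = 1 − Φ((5 − d)/SE). At d = 5 this is 1 − Φ(0) = 50%. SE cancels, so neither n nor SD matters, and more patients would not change it.
On the stricter reading (lower 95% limit above 5), the probability is Φ((d − 5)/SE − 1.96), which at d = 5 is Φ(−1.96) = 2.5%.

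**3. Other true differences, 40 per arm.**

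| | SD 4.5 (SE 1.006) | SD 6.2 (SE 1.386) |
|---|---|---|
| P(observed ≥ 5), true 4 | 16% | 24% |
| P(observed ≥ 5), true 5 | 50% | 50% |
| P(observed ≥ 5), true 6 | 84% | 76% |
| True difference for a 95% chance: 5 + 1.645 × SE | 6.66 | 7.28 |
| True difference for a 95% chance that the lower limit exceeds 5: 5 + 3.605 × SE | 8.63 | 10.0 |
| Smallest observed difference significant against zero: 1.96 × SE | 1.97 | 2.72 |

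If all 50 per arm are retained, the true difference for a 95% chance is 6.48 (SD 4.5) or 7.04 (SD 6.2).

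**4. The zone without a stated conclusion.** Observed differences from about 2.0 (SD 4.5) or 2.7 (SD 6.2) up to 5 degrees are significant against zero but fail the criterion. For illustration, an observed 4.5 with SD 4.5 has a 95% CI of 4.5 ± 1.97, or 2.5 to 6.5. Zero is excluded and 5 is not, yet the criterion is not met.

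**The case against.** The best defence is that superiority over zero is already in the text: the purpose sentence in Objectives, the design statement in Sample size and the ordinary tests in Statistical methods all point to it. Read that way, 5 degrees is a planning difference and relevance yardstick, and the fault is loose wording in Outcomes and Objectives. Asking for a minimum relevant estimate from a burdensome treatment is also legitimate, and a 50% chance at the threshold comes with any such rule. This much stands: the 5-degree benchmark is not itself wrong. But Outcomes states it as the criterion, no other criterion for effectiveness is given, and the only power figure belongs to a different question.

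Three stronger readings are not supported.

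- *That bracing would be called ineffective half the time.* Outcomes says potentially effective, and does not say only if. Nothing states that a result below 5 would be reported as ineffective. What can be said is that such a result fails the one stated criterion. The word observed is also an inference, though a rule on the arms' means can be applied only to observed means, and the alternative reading gives 2.5%.
- *That failing the 5-degree criterion would end screening.* The Discussion does say "If bracing doesn't prove to be effective, a screening program is not applicable", but the argument there is about burden of proof: an effective early treatment is a precondition for screening. It does not cite the 5-degree criterion. Question 3 is a conditional economic question, not a decision rule.
- *That the trial is too small.* Against zero, the stated inputs give more than 95% power.

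**Conclusion.** The point holds as a mismatch between the stated power and the stated criterion. The firm figure is 50% at a true 5 degrees against the 95% a reader would assume; it requires only that the estimated difference be distributed symmetrically around the true one. The remaining figures depend on the SD and on 40 per arm analysed: a true difference of about 6.7 (SD 4.5) to 7.3 (SD 6.2) for a 95% chance, and a zone without a stated conclusion running from about 2.0 or 2.7 up to 5 degrees. Allocation, data collection and the planned comparisons are unaffected. What is wrong is how the primary conclusion is defined and the power claimed for it.

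**What to change.** Choose one of two wordings and use it in the Abstract, Objectives, Outcomes and Sample size.

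1. State the primary hypothesis as superiority over zero, report the mean difference in progression with its 95% CI, and describe 5 degrees as the planning difference and relevance benchmark.
2. Keep the 5-degree criterion, and state that its chance of being met is 50% at a true 5 and 95% only at a true difference of about 6.7 to 7.3 degrees with 40 per arm.

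In either case, state in advance conclusions that do not overlap:

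- CI above 0 and reaching 5 or more: bracing reduces progression, and a 5-degree benefit is not excluded.
- CI above 0 and entirely below 5: a real benefit, but smaller than 5 degrees.
- CI including 0 and entirely below 5: no benefit shown, and a 5-degree benefit excluded.
- CI including both 0 and 5: inconclusive.
- For completeness, CI entirely below 0: more progression with bracing.

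An inconclusive result should not be presented as evidence that bracing is ineffective when research question 3 is answered. With 40 per arm that result needs a CI at least 5 degrees wide, so an SD of at least 2.5 / (1.96 × √(2/40)) = 5.7. It cannot arise at SD 4.5 but can at 6.2, or with fewer patients retained.

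The cost is rewording. No extra patients, visits or data are needed.

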## Background

Idiopathic scoliosis (IS) is defined as a lateral curvature of the spine of unknown origin with a minimal Cobb angle of 10 degrees. The Cobb angle is the angle between the upper most inclined vertebra and the lower most inclined vertebra. Besides a lateral curvature of the spine, there is a fixed rotation of one or more vertebrae and a rotational deformation of that vertebra. Once the curvature shows progression and exceeds a Cobb angle of about 20 to 25 degrees, the curvature is not likely to disappear spontaneously. Progression of the curvature usually occurs just before or during the growth spurt [1].

IS patients who are not fully grown and who have Cobb angles over 20–25 degrees with established progression of at least 5 degrees are usually treated with a brace [1]. A brace is a close fitting device applied to the trunk to try and prevent further progression of the curvature and thereby ultimately the need for surgical treatment. Surgical treatment may become necessary when not fully grown patients reach Cobb angles over 45–50 degrees [1].

Although many orthopedic surgeons feel that bracing might slow down progression of IS and some believe that reduction of the lateral curvature is also feasible, the effectiveness of early treatment of IS with a brace has not yet been established. No randomized controlled trial (RCT) on bracing for IS can be found in the Cochrane library or in PubMed. The majority of the studies are retrospective cohort studies. Some authors suggest that their results confirm that the brace is effective [2-4]; others conclude that the effectiveness of bracing is doubtful or recommend a RCT [5-8]. Some studies were performed without a control group; these study results are compared with results on the natural history from other studies. Another problem in the interpretation of the results of these studies is that they lack consistency regarding both inclusion criteria and the definitions of brace effectiveness [9]. In practice, there is currently no trial evidence that bracing IS patients is better than observation and watchful waiting [10-12]. Several Dutch orthopedic surgeons have reached consensus that a RCT is justified under the condition that the patients included are in an early stage of the clinical course of scoliosis [5]. In collaboration with these orthopedic surgeons, we formulated the current study design.

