### Intervention group

Early treatment of IS consists of wearing a brace that is intended to prevent the curvature from worsening. Patients in the intervention group will initially be braced for two years. The orthopedic surgeon will refer the patients to a qualified certified prosthetist orthotist who will measure, make and fit the brace. Each brace will be measured and modified individually for each patient to fit and correct her/his curvature. She/he will be advised to wear the brace every day for 18–23 hours. Boston braces will be used for all patients; this brace is used the most in the Netherlands. Patients are usually advised to attend physical therapy for muscle training and to correct body posture. Physical therapy alone is not expected to prevent further progression of the curvature [11]. Therefore, patients are free to choose whether or not they will attend physical therapy.

Although some orthopedic surgeons prefer to keep the patients in the hospital for a few days to allow them to become used to wearing the brace, others do not. The orthopedic surgeons are allowed to apply their own protocol concerning this hospital admission.

In case patients of the intervention group reach Cobb angles that require surgery, they can be operated.

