### Control group

Patients in the control group will initially not be braced during the two study years, unless their curvature shows more than 10 degrees progression compared to the Cobb angle at inclusion. In this case, the orthopedic surgeon, patients and their parents could decide to start brace treatment. The patients in the control group are allowed to attend physical therapy if they want to, because physical therapy alone will not prevent further progression of the curvature.

In case patients of the control group reach Cobb angles that require surgery, they can be operated.

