### Statistical methods

The intervention and control group will be compared based on the 'intention to treat' principle. Differences in Cobb angle between the two groups and other continuous parameters will be measured using parametric or non-parametric tests (depending on skewness) for group comparisons. Categorical parameters will be compared by the Chi-square test. Logistic regression will be applied to measure the treatment effect (yes/no progression) adjusting for covariates. Since we have 4-month measurements on Cobb angles in both arms, progression in Cobb angle will be analyzed with a linear mixed effect model, where we will assume a simple compound symmetry structure. This may be particularly important for extrapolations to follow-up periods longer than 2 years after entry.

When a patient in the control group had to be braced before the end of the follow-up (because of a more than 10 degree progression of the curvature), her/his Cobb angle at the moment of commencing treatment will be considered as final outcome and will be included in the analysis.

In a second analysis, we will perform Kaplan-Meier analyses with these 'progression to more than 10 degrees' as events, in both arms (intention-to-treat).

Stratified analysis will be done to evaluate whether curve type, brace compliance, Cobb angle at inclusion and Risser sign at inclusion influence the effectiveness of brace treatment. Using logistic regression we will also evaluate whether brace compliance depends on gender and age.

Health-related quality of life and utilities will be compared between the intervention and control group. This will be done by basic descriptive statistics. Depending on the distribution of the data, parametric or non-parametric tests will be used.

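### Operated patients are scored at two years like everyone else, so a surgical correction would count as improvement; the number affected is probably small and the net direction is uncertain.

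*Protocol article*

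**What the plan says.** Surgery during the two study years is permitted in each arm. Under Intervention group: "In case patients of the intervention group reach Cobb angles that require surgery, they can be operated". Under Control group: "In case patients of the control group reach Cobb angles that require surgery, they can be operated". The Background section gives the range in which this arises: "Surgical treatment may become necessary when not fully grown patients reach Cobb angles over 45–50 degrees".

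Under Outcomes, the primary value is set for every participant: "Two years after date of randomization the primary outcome measure, progression in Cobb angle, will be established in each patient". Bracing is to be judged potentially effective if "the mean progression of the abnormal curvature in the intervention group is at least 5 degrees less than in the control group".

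Statistical methods specifies intention to treat and one exception to the two-year value. It begins "When a patient in the control group had to be braced before the end of the follow-up" and takes that control's Cobb angle at the start of bracing as the final outcome. No counterpart exists for surgery in either arm. The linear mixed model on the four-monthly angles is described without any rule for visits after an operation.

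**The concern.** Surgery straightens the curve. If the month-24 film of an operated patient is scored like any other, a patient who progressed into the surgical range is entered with a large negative progression. The recorded value then has the wrong sign for the question asked, since the stated purpose of bracing is to slow curvature and so prevent surgery in some patients.

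The plan also treats a change of treatment unevenly. A control who progresses by more than 10 degrees and is braced is held at the progressed angle. A braced patient with the same course who is operated has no such rule. What is at stake is the primary mean comparison and the 5-degree criterion attached to it.

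**Working it through.** **Inputs from the article.** Baseline 22 to 35 degrees; two-year change given as "the range in change will be 0–15 ± 2 degrees" and assumed uniform; SD about 4.5 degrees; 40 patients per arm (all under Sample size). Surgery over 45–50 degrees (Background). Visits every four months (Follow-up). Brace option for controls above 10 degrees of progression (Control group).

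**Assumptions not in the article.** Post-operative angle 15 to 25 degrees; surgical threshold varied from 45 to 48 degrees; baseline uniform and independent of change; linear progression over 24 months.

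**The plan's own figures.** It gives none for surgery. Its SD is roughly recovered: a uniform 0–15 change has SD 15/√12 = 4.33. The standard error of the difference is then 4.5 × √(2/40) = 1.0 degree. The 40 per arm is taken as given; how it was derived is a separate matter.

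**Step 1: effect of one operated patient.** The baseline cancels, so the shift in the arm mean is (pre-operative angle − post-operative angle)/40.
- Operated at 48: (48 − 25)/40 = 0.58 to (48 − 15)/40 = 0.83 degrees.
- Operated at 45: (45 − 25)/40 = 0.50 to (45 − 15)/40 = 0.75 degrees.

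**Step 2: how many could be operated.** An operation can distort the month-24 film only if it precedes that film. Suppose surgery is indicated by month 20. The largest change by then is 15 × 20/24 = 12.5, so the highest angle is 35 + 12.5 = 47.5. With T the threshold, the probability of reaching it is (47.5 − T)²/2 divided by 13 × 12.5 = 162.5.
- T = 45: 3.125/162.5 = 1.9%, or 0.77 of 40.
- T = 47: 0.125/162.5 = 0.08%, or 0.03 of 40.
- T = 48: none.

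The upper extreme ignores timing and operates on everyone whose month-24 angle is 45 or more: (50 − 45)²/2 = 12.5, divided by 13 × 15 = 195, is 6.4%, or 2.6 of 40. At 48 the same calculation gives 2/195 = 1.0%, or 0.4 of 40.

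**Step 3: net direction with no true brace effect.** Here every braced patient reaching T by month 20 is operated, and every control above 10 degrees is braced.
- *Controls fixed at brace start.* On linear progression, those with a two-year change above 12 pass 10 degrees by month 20 (12 × 20/24 = 10), and none has passed it by month 16 (15 × 16/24 = 10). They are 3/15 = 20% of controls and lose 4/24 of their change, on average 13.5/6 = 2.25 degrees. The control mean falls by 0.20 × 2.25 = 0.45, which works against the brace.
- *Braced patients operated at T = 45.* Their mean baseline is 35 − 2.5/3 = 34.2. Their mean change is 12.5 − 2.5/3 = 11.7 at month 20, which would be 14.0 at month 24. A post-operative angle of 20 replaces +14.0 with −14.2, a gap of 28.2; 28.2 × 0.0192 = 0.54 in the brace's favour. Post-operative angles of 25 and 15 give 0.45 and 0.64.
- *Net.* At T = 45: 0.54 − 0.45 = about +0.1 degrees (0.0 to +0.2 over the post-operative range). At T = 47 to 48 almost nobody is operated and the net is about −0.4 to −0.5, against the brace. A simulation of this scenario with 40 per arm agreed.

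**The case against.** **It is an inference.** The article never says that post-operative films are scored, and its one explicit rule uses the angle before the change of treatment. A journal article may also leave rare events to a fuller document. This stands as a caution. But the article does fix the primary value for each patient and does write a rule for one change of treatment. Leaving out the other change that it permits makes that rule incomplete, which is more than condensed detail.

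**The size is limited.** This stands; see step 2. Non-parametric tests, allowed under skewness, would further limit the pull of one or two extreme values.

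**Other analyses catch these patients.** Largely true. Going from at most 35 to over 45 degrees means passing 10 degrees of progression, so the Kaplan-Meier analysis already counts them as events. Adding surgery as an event there would be nearly redundant. That analysis is secondary, however, and does not correct the primary mean.

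**A stronger reading is tempting.** A reader might infer a sure bias in the brace's favour, with its failures becoming its best results. If everyone at 45 degrees or more at month 24 in the brace arm is scored after surgery, and controls above 10 degrees are capped at 12, a null simulation gives a spurious benefit of 1.1 to 1.7 degrees and favours the brace in 16–21% of trials, against a nominal 2.5%. The documents do not support this as the expected result. It lets a month-24 angle trigger surgery that precedes the month-24 film. With a threshold of 47 the same simulation falls to 0.2–0.5 degrees and 3.6–4.1%. Bracing of progressed controls is optional, so a control operated without a brace is flattered in the same way, and if both arms are scored alike the null bias vanishes. If bracing works, more operations would be expected among controls, which would bias against it.

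**Conclusion.** The point holds as a gap in the outcome rule. Followed literally, the plan records an operated patient as improved, and its rule for a change of treatment applies to one arm and one event only. Per operated patient the shift is about 0.6 to 0.8 degrees in an arm mean, if surgery is at 48 degrees and leaves 15 to 25, against a standard error of about 1.0 and a criterion of 5 degrees.

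The total effect is probably small: about 0 to 1 operated patient per 40 on the plan's ranges with linear progression, and 2 to 3 only if all patients at 45 degrees or more were operated before the last film. Faster early progression would raise the lower figure. The net direction cannot be settled from the article, and a firm claim that the trial is tilted towards the brace is not supported. The change is still worth making, because the per-patient value is wrong whichever arm it falls in and the remedy is cheap.

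**What to change.** Add one rule to Statistical methods, identical in both arms: for a patient operated before month 24, the final outcome is the last Cobb angle before surgery, read by the blinded assessors, and post-operative visits are excluded from the linear mixed model. Add a sensitivity analysis that ranks surgery as the worst outcome, and report the number operated in each arm.

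The cost is a few sentences. The films are already taken every four months and read blind, and each visit already records whether surgery is indicated. No clinical management changes. The small downside is that the pre-operative angle is observed before month 24, so it omits any progression that would have followed; the sensitivity analysis shows whether this matters.
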